### Analysis Plan

The statistical analyses used to test each of our hypotheses are described below and summarized in Table 2. We will conduct the exploratory cost-effectiveness analysis in Stata (StataCorp LLC; [69]) and all other statistical analysis in R (R Foundation for Statistical Computing; [70]). We will report descriptive statistics (mean and SD if normally distributed, median and range if not) of all the variables included in the analyses. For all the analyses involving linear regression, we will check if the assumptions of linear regression are met by inspecting the residual plots for linearity, homogeneity of variance, normality, independence of residuals, and collinearity. If basic assumptions are not met, we will attempt to meet them via variable transformation, and failing that, we will use robust regression methods.

To ensure we only analyze responses from genuine participants, we will exclude participants from the study who give impossible or mutually incompatible responses as soon as they are detected [71]. As the primary strategy to handle missing data, the longitudinal constrained analysis assumes that the probability of missing outcome data is not related to the missing data but to some of the observed data in the model (missing at random [MAR]). Our models will use a restricted maximum likelihood (REML) estimator to handle missing data. The use of the REML estimator will enable us to effectively handle the potential bias introduced by differential attrition, as it allows for the estimation of unbiased fixed-effects coefficients and appropriately accounts for the variability introduced by random effects.

In addition, we will perform sensitivity analysis to assess how robust our analysis of the primary outcome is to deviations from MAR. We will calculate censoring weights by investigating the baseline and time-varying predictors of attrition, including engagement and response to follow-up factors. We will then recalculate the primary analysis with inverse probability of censoring weighting [72].

For hypothesis 1, we will perform linear mixed model analysis of the fixed effect of the amount of meditation in the past month on quality of life in the past week (EQ-HWB-9), controlling for the potentially confounding baseline factors of age, caring status, education, mental health diagnosis, commitment to meditation practice, and membership of a meditation practice community at baseline. This model will allow us to assess how meditation as practiced by our participants under naturalistic conditions contributes to their quality of life, controlling for baseline differences related to time available for practice, symptom severity, motivation, and social support. If we detect an effect of meditation practice, we will perform sensitivity analysis to examine how robust this effect is to time-varying confounders by using inverse probability weighting of meditation in the last month to examine if the association would still be present if practice that month had varied independently of prior practice and benefit.

For hypothesis 2, we will perform linear mixed model analysis of the fixed effect of the amount of meditation in the past month on mental well-being in the past 2 weeks (SWEMWBS), controlling for the potentially confounding factors of age, caring status, education, mental health diagnosis, commitment to meditation practice, and active membership of a meditation practice community at baseline. If we detect an effect of meditation practice, we will again perform time-varying confounding sensitivity analysis with inverse probability weighting.

For hypothesis 3, we will add the variable capturing whether participants practiced secular meditation traditions (with no more than one month of reported practice in a spiritual tradition) versus engaging in spiritual traditions and its interaction term with the amount of meditation to the model for hypothesis 1. This initial analysis will allow us to assess whether predominantly secular meditation has a differential effect from meditation that incorporates spiritual practices, as practiced in real-life contexts, while retaining sufficient power. If we detect an effect, we will perform further exploratory analysis into what may be driving this difference. We will also describe the groups in terms of meditation practice characteristics, including proportion of practice types and social context.

For hypothesis 4, we will add the secular versus spiritual variable and its interaction term with the amount of meditation to the model for hypothesis 2.

To address aim 5, we will conduct an exploratory cost-effectiveness analysis using participants who did not continue meditating as a comparator to participants with ongoing meditation practice, while accounting for relevant confounding factors. We will use the EQ-HWB-9 to measure outcomes, applying index values from the United Kingdom pilot value set over time to create QALYs [60]. Costs will include those for mental health service use (psychological support) across one year plus costs of meditation practice. To calculate the incremental cost-effectiveness ratio (ICER) from a public health perspective, we will calculate the difference in costs between the low- and high-meditation dosage groups and divide by differences in QALYs. The ICER represents the additional cost of the intervention for each additional unit of health benefit gained. We will investigate the cost-effectiveness of the ICER against thresholds of the 4 included countries, as available, to determine how likely the intervention will be cost-effective from a public health perspective. Issues of confounding will be addressed through statistical adjustments as per the main analysis, and we will conduct relevant scenario analyses. We will conduct deterministic (one-way) sensitivity analysis to estimate the impact of uncertainty around effects by varying output and cost parameters, displayed on tornado graphs. We will conduct probabilistic sensitivity analysis to explore the combined parameter uncertainty over 10,000 iterations, displayed on a cost-effectiveness plane.

To address aim 6, we will estimate the incidence of participants first reporting adverse effects by reporting the proportion and confidence intervals of first adverse experiences that also impaired participants’ daily function. We will also report descriptive statistics of the frequency, severity of impairment of daily function, and duration of impairment of meditation-related challenging experiences and MRAEs.

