### Measures

A schedule of measures is shown in Table 3 and described in detail below.

Meditation practice frequency and duration will be assessed weekly. Participants will be asked how many days they practiced in the past week, the average number of sessions per day, and the average minutes per session. This is a weekly modification of the timeline followback method, which is the gold standard for reporting in substance use literature, and has been validated for exercise reporting [32] and online administration [56]. We have also validated this question format against a log of meditation timer practice data [32]. Weekly measurement supports accurate reporting in similar methods [57], while allowing us to calculate the amount of meditation each month. This will be our independent variable.

Meditation practice characteristics, including type (eg, meditation with movement such as walking meditation or mindful observation such as observing thoughts or emotions), guided versus unguided sessions (eg, “I work with a teacher or instructor” or “My practice is self-guided”), and social context of their practice (eg, “I practice in a group” or “I practice alone”), will be recorded monthly. These measures will be used to describe the sample by reporting the frequency of each practice type and context reported by participants over one year.

Secular or spiritual meditation practice will be assessed at baseline and monthly by a single item (“In the past month, what meditation traditions have you practiced in?”). Participants will be divided into 2 groups at follow-up; those who both nominated secular meditation as their tradition at baseline and reported a maximum of one month of practice in any spiritual tradition over the follow-up period, versus all participants who practiced in spiritual traditions for 2 months or more during the year. This division will facilitate investigating if those meditation practitioners who practice in spiritual traditions experience the same effects as secular practitioners, while allowing for some dabbling in different traditions by participants. This will be a covariate.

Commitment to meditation practice will be assessed at baseline with a single item (“How committed are you to practicing meditation?” Rate 1‐10). This will be a covariate.

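### The check offered for departures from missing at random uses only observed predictors of dropout, so it cannot show what happens if dropout depends on the unseen EQ-HWB-9 score

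*Protocol article*

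**What the plan says.** All statements are in the protocol article.

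- **Assumption (Analysis Plan).** The primary strategy assumes that "the probability of missing outcome data is not related to the missing data but to some of the observed data in the model". This is MAR, stated for outcomes and relative to the variables in the model.
- **Estimator (Analysis Plan).** "Our models will use a restricted maximum likelihood (REML) estimator to handle missing data". The estimator is said to "effectively handle the potential bias introduced by differential attrition, as it allows for the estimation of unbiased fixed-effects coefficients".
- **Sensitivity analysis (Analysis Plan).** Its stated purpose is to see how far the primary result withstands departures from MAR. Its content is: "We will calculate censoring weights by investigating the baseline and time-varying predictors of attrition, including engagement and response to follow-up factors". Then: "We will then recalculate the primary analysis with inverse probability of censoring weighting". No other missing-data analysis is named.
- **Exposure (Measures).** Practice is reported weekly, "allowing us to calculate the amount of meditation each month". That monthly amount is the fixed effect of interest in the Hypothesis 1 model.
- **Loss (Sampling Plan, Hypothesis 1).** A 20% loss to follow-up over one year is expected. Table 2 also provides for a follow-up survey after two months without practice reports.

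**The concern.** A departure from MAR, in the usual sense, means that whether a score is missing depends on the score itself, even after conditioning on everything observed. Censoring weights are computed from observed variables and are valid only if no such dependence remains. They therefore replace one MAR-type condition with a wider one.

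In this cohort, participants whose quality of life worsens may stop practising and stop answering. The documents do not say that this will happen, but it is the case that such a sensitivity analysis is meant to cover. If the weighted and unweighted results agree, readers could take the primary result as checked against non-random dropout when it has not been.

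The secondary issue is the breadth of the REML sentence. A likelihood mixed model uses incomplete outcome series, but it does not recover a row whose covariate is missing. Table 3 collects practice weekly and EQ-HWB-9 monthly, so a month can have an outcome and an incomplete practice amount.

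**Working it through.** The plan gives no figure on this point to reproduce. The check is a comparison of assumptions, followed by a simulation.

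**1. Assumptions side by side.** Let Y(t) be EQ-HWB-9 at month t, M the observed data in the outcome model, and H the wider observed history used for the weights.
- Primary model: P(drop at t | M, Y(t)) = P(drop at t | M).
- Weighted analysis: P(drop at t | H, Y(t)) = P(drop at t | H), with weight 1 / product over s ≤ t of P(stay at s | H).
- Departure from MAR in the usual sense: P(drop at t | H, Y(t)) still depends on Y(t).

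The weights contain no term for Y(t) among those who left, and no parameter that can be varied to represent it.

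**2. Simulation of dropout.** Assumed: 12 months, true slope 0.5, random-intercept SD 1, residual SD 1, 20,000 participants, 15 replicates. The mixed model was fitted by generalised least squares at the true variances. The weighted analysis was weighted least squares with pooled-logistic weights. Monte Carlo standard errors were at most 0.0008 (mixed) and 0.0022 (weighted).

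| Dropout depends on | Retained | Mixed | Weighted |
|---|---|---|---|
| Previous observed outcome | 85.8% | 0.500 | 0.499 |
| Previous observed outcome | 70.5% | 0.501 | 0.502 |
| Observed engagement variable outside the outcome model | 85.5% | 0.492 | 0.499 |
| Observed engagement variable outside the outcome model | 69.6% | 0.484 | 0.502 |
| Unseen current outcome | 81.5% | 0.490 | 0.475 |
| Unseen current outcome | 65.1% | 0.482 | 0.460 |

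In the last two rows the mixed model is low by 0.010/0.5 = 2% and 0.018/0.5 = 3.6%. The weighted analysis is low by 0.025/0.5 = 5% and 0.040/0.5 = 8%. Weighting does not remove the bias.

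A run with 600 participants, 60 replicates, REML, stronger dropout and weights capped at their 99.5th percentile gave:
- engagement-driven dropout (57.3% retained): mixed 0.473, weighted 0.467;
- dropout on the unseen outcome (51.9% retained): mixed 0.469, weighted 0.428.

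So the repair in the engagement rows of the table is not guaranteed under heavy dropout with capped weights.

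**3. Missing practice amounts.** Same model, 600 participants, REML on complete rows.
- Missingness dependent on the outcome (72.7% of rows kept): slope 0.421, low by 0.079/0.5 = 15.8%.
- Missingness dependent on practice only: slope 0.502, no bias.

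**4. Scale for a delta.** The Sampling Plan takes 2.25 points as the EQ-HWB-9 change that goes with improved mental health, and a 4.5-point high-versus-low difference at the last time point. Worsening the 20% expected to be lost by 2.25 points moves the overall final mean by 0.20 × 2.25 = 0.45 points. For the high-versus-low contrast, with three equal dose groups (assumed), the shift is 0 if losses are evenly spread. If every loss falls in the high or the low group, that group loses 3 × 20% = 60%, and the shift is 0.60 × 2.25 = 1.35 points, or 30% of 4.5. This is a range, not a forecast.

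**The case against.** **REML does what it is credited with for outcomes.** The sentence before the REML claim confines the assumption to outcome data, and under that assumption the mixed model is unbiased (0.500 and 0.501). A reader might infer that the plan has no protection against attrition at all. The documents do not support that.

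**The weights do test something.** The article words MAR relative to data in the model. The engagement and response-to-follow-up factors in the weights are not listed in the Hypothesis 1 model, so the weighting relaxes that narrower assumption, and the table shows it can repair such bias. This stands, and it is why the weighting should be kept. It does not rescue the label: dropout on the unseen score remains unexamined.

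**An article may leave detail to the full plan.** This stands for the rule on partly reported months, whose absence is no error in itself. It does not cover the sensitivity analysis, because the article names both purpose and method and the two do not match.

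**Large losses of exposure data cannot be inferred.** A reader might reason that with 90% or 80% weekly response only 0.90^4 = 66% or 0.80^4 = 41% of months are complete, so 34% to 59% of rows are lost or understated. The article gives no weekly response rate and no deletion or summing rule. The calculation also needs independent weekly response; clustered non-response leaves more complete months at the same average. A reader might also infer that the slope is biased because people who stop practising stop reporting. Deleting rows on practice alone did not bias it (0.502).

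**No material bias has been shown.** Near the planned loss, the mixed model was 2% low under assumed strengths. This stands: the case rests on a promised check that is not delivered, not on a demonstrated error in the result.

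**Conclusion.** The concern holds in this form: the article promises an assessment of departures from MAR, and the one analysis it names for that purpose is itself valid only under a MAR-type condition on a wider set of observed variables. No stated analysis lets dropout depend on the unseen EQ-HWB-9 score. This follows from the definition of the weights and does not rest on the simulation, which only illustrates it.

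The secondary point is one of scope. The claim that REML deals with missing data should be limited to outcomes, since rows with no monthly practice amount are not recovered. Missing practice reports bias the complete-row slope when missingness depends on the outcome given practice and covariates; otherwise the cost is lost information. The size of either bias cannot be derived from the documents.

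This should be corrected before analysis. It does not invalidate the design or the primary model.

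**What to change.** 1. Keep the censoring weights, and describe them as a check on dropout explained by measured predictors outside the outcome model.
2. Add a delta-adjusted (pattern-mixture) sensitivity analysis for the primary outcome. Impute EQ-HWB-9 after dropout, worsen it in steps up to and beyond 2.25 points (in the direction that means worse quality of life under the scoring used), refit the model, and report the step at which the conclusion changes. Someone who leaves usually stops supplying practice data too, so state what practice amount is assumed or imputed for those months; the effect of a delta on the slope depends on it.
3. Limit the REML sentence to missing outcomes under MAR.
4. State that an unreported week is missing, not zero. If incomplete months are common, multiply impute weekly practice using outcomes and covariates.

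Other methods that let dropout depend on unseen scores would also serve for item 2. The cost is a few sentences of plan wording and modest programming, with no new data. Results are expected in January 2028, so the change can still be prespecified.

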Finally, the study aims to document the incidence and impact on daily function of any challenging, difficult, or distressing meditation-related experiences (Aim 6). Meditation-related adverse effects (MRAEs) will be defined as any challenging, difficult, or distressing meditation-related experiences that impact everyday functioning. Our aims, hypotheses, and possible interpretations are summarized in Table 1 below.

**Table 1. T1:** Protocol Design table.

Question	Hypothesis	Sampling plan (eg, power analysis)	Analysis plan	Interpretation given to different outcomes
Does regular meditation practice after initial instruction increase quality of life?	The amount of meditation practice during approximately the first year predicts practitioners’ quality of life, such that a greater amount leads to greater quality of life.	A total number of 522 gives 95% power to detect the variance in quality of life (EQ-HWB-9^a^) explained by monthly meditation practice observed in linear mixed model analysis, at a 2-tailed significance level of 0.05, accounting for an estimated 20% loss to follow-up.	Linear mixed model of the fixed effect of the amount of meditation in the past month on quality of life in the past week (EQ-HWB-9), controlling for the confounding factors of age, caring status, education, mental health diagnosis, commitment to meditation, and membership of a practice support community at baseline.	A positive/negative and statistically significant association between the amount of meditation in the past month on quality of life and in the past week will suggest that regular meditation practice after initial instruction increases/decreases quality of life in a linear fashion. A nonsignificant association will suggest an absence of evidence for either of these effects.

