Quality of life will be assessed at baseline, monthly, and one year, using the 9-item EQ Health and Wellbeing (EQ-HWB-9) instrument [58]. The EQ-HWB-9 captures mental (eg, depression and cognition), physical (eg, pain), and social (eg, loneliness) aspects of quality of life for the past 7 days, on a 5-point Likert scale from 1 (No difficulty) to 5 (Unable). Previous responsiveness to change analysis indicates that the EQ-HWB-9 detects meaningful changes in both mental and physical health measures [59]. This will be our primary outcome. The EQ-HWB-9 also allows for the calculation of quality-adjusted life years (QALYs), a standard measurement in health decision-making, and thus allows for the comparison of both effectiveness and cost-effectiveness with many other interventions and standard treatments [60].

Mental well-being will be assessed at baseline, monthly, and one year using the Short Warwick-Edinburgh Mental Well-Being Scale (SWEMWBS) [61,62]. The SWEMWBS includes 7 items that assess mental well-being over the past 2 weeks, on a 5-point Likert scale from 1 (None of the time) to 5 (All of the time). This will be our secondary outcome. The items in the SWEMWBS are positively worded (eg, “I’ve been feeling optimistic about the future”) and aim to capture variation in the flourishing side of the well-being spectrum, which will supplement detailed variation in the quality of life deficits captured by the EQ-HWB-9. Previous analyses of responsiveness to change indicate that the SWEMWBS detects individually meaningful improvement across a variety of mental health measures [63].

MRAEs will be measured at baseline, one year, and monthly, using the 3-item MRAEs measures [42]. The first item asks participants to indicate the frequency of any challenging, difficult, or distressing meditation-related experiences, with options ranging from “never” to “frequently.” The second item assesses the level of impairment caused by these experiences on the participant’s ability to function, with options ranging from “not at all” to “severely.” The third item asks about the duration of the impairment, with options ranging from “1 day or less” to “1 year or longer.”

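### The past-month practice total contains the outcome's own recall window, so same-period feedback can bias H1 and H2 in either direction, and the planned weighting does not address it

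*Protocol article*

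**What the plan says.** For hypothesis 1 the Analysis Plan fits a linear mixed model of "the amount of meditation in the past month on quality of life in the past week", adjusted for baseline factors only. For hypothesis 2 it fits the "fixed effect of the amount of meditation in the past month on mental well-being in the past 2 weeks", with the same kind of adjustment.

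The Measures section confirms the windows. Practice is reported weekly, "while allowing us to calculate the amount of meditation each month". The EQ-HWB-9 covers "aspects of quality of life for the past 7 days". For the secondary outcome, "The SWEMWBS includes 7 items that assess mental well-being over the past 2 weeks". No lag is stated, and the recall window is not left out of the exposure.

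If an effect is found, a sensitivity analysis by inverse probability weighting asks whether the association would remain "if practice that month had varied independently of prior practice and benefit". Table 1 fixes the reading in advance: a significant association "will suggest that regular meditation practice after initial instruction increases/decreases quality of life in a linear fashion". The mental well-being row is worded in the same way. The limitations at the end of the Discussion name self-selection, expectancy and placebo, but not reverse causation.

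**The concern.** Exposure and outcome share calendar time. A participant who has a bad week and skips practice, or who practises more because the week is bad, creates an association between that week's practice and that week's score without any effect of meditation. The primary model has only baseline covariates and cannot separate this from an effect. The weighting balances practice on what came before the month, so it leaves feedback within the month untouched. At stake is the main claim of the study: Table 1 turns a significant coefficient into a directional statement about what practice does.

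**Working it through.** **Overlap.** Taking a month as four weeks, EQ-HWB-9 recall is 7/28 = 25% of the exposure window and SWEMWBS recall is 14/28 = 50%. The exact alignment of weekly reports with the monthly survey is not spelled out, so these are approximations.

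**Inputs from the Sampling Plan.** 435 participants before the dropout allowance, 12 monthly outcomes, SD 7.0, two-sided alpha 0.05. Higher scores are treated as better, as that section does.

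**Assumptions not in the documents.** SD between persons 5.0 and within persons 4.9 (25 + 24.01 = 49.01, and 7.0² = 49); stable practice differences between persons with SD 1; weekly practice deviations with SD 1; same-week correlation g between state and practice; week-to-week autocorrelation rho of state. Practice has no effect on the outcome.

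**Spurious slope by hand, one-week recall, rho = 0, g = 0.10.**
- Within-person covariance: 4.9 × 0.10 / 4 = 0.1225. Within-person variance of the four-week mean: 1/4. Within-person slope: 0.1225 / 0.25 = 0.49.
- The random-intercept model pools this with a between-person slope near zero. Information per person: within, 11 × 0.25 = 2.75; between, [24.01 / (24.01 + 12 × 25)] × 12 × (1 + 0.25/12) = 0.91. Weight on the within part: 2.75 / 3.66 = 0.75.
- Slope: 0.49 × 0.75 ≈ 0.37. Standard error: √[24.01 / (435 × 3.66)] ≈ 0.123. z ≈ 3.02, so rejection ≈ Φ(3.02 − 1.96) ≈ 86%.
- At g = 0.05, z ≈ 1.51 and rejection ≈ 33%.

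**Simulation under the same null (300 runs per setting, one-week recall), share of runs with p < 0.05.**

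| g | rho | Planned model | Weighted, one month | Weighted, cumulative | Overlap week left out | Previous month, adjusted for prior outcome |
|---|---|---|---|---|---|---|
| 0 | 0 | 5% | 4% | 9% | 6% | 6% |
| 0.05 | 0 | 33% | 23% | 12% | 4% | 5% |
| 0.10 | 0 | 88% | 63% | 31% | 4% | 6% |
| 0.10 | 0.5 | 100% | 99% | 84% | 84% | 6% |
| 0.20 | 0.5 | 100% | 100% | 100% | 100% | 24% |
| −0.10 | 0 | 86% | 72% | 45% | 7% | 8% |

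Other simulations, with 435 or 480 participants and outcome ICC 0.5 or 0.7, gave 30–43% at g = 0.05 and 88–90% at g = 0.10 for the planned EQ-HWB-9 model without carry-over.

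**Weighting.** At g = 0.10 and rho = 0 the spurious estimate is 0.37 in the planned model, 0.42 with one-month weights and 0.41 with cumulative weights. The bias does not shrink; rejection falls because standard errors widen.

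**Direction.** At g = −0.10 and rho = 0 the estimate is −0.38.

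**Two-week recall (SWEMWBS-type overlap, run on the EQ-HWB-9 scale).** At g = 0.10 the planned model rejects in 100% of runs. At g = 0.05 it rejects in 61% to 92%, depending on whether the correlation is defined for each week's state or for the two-week outcome.

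**Leaving out the overlap.** At g = 0.10 and one-week recall, rejection is about 4% at rho = 0, 28% at 0.3, 81–84% at 0.5 and 100% at 0.7. At rho = 0.5 the spurious slope falls from 0.67 to 0.32.

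**Previous month's practice, adjusted for the outcome at the end of that month.** At rho = 0.5 the estimate is −0.06 at g = 0.10 and −0.13 at g = 0.20. In every feedback setting run, its residual bias was small and opposite in sign to that of the planned model. With two-week recall at g = 0.10 and rho = 0.5 it rejected in 15% of runs.

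**Scale.** The Sampling Plan's group gains of 0, 2.25 and 4.5 points, averaged over a linear rise, differ by 1.125 per step. With three equal groups (SD √(2/3) = 0.816) that is 0.92 points per SD of dose, or 2.25 × 0.816 = 1.84 at the last time point. The spurious slope of 0.37 per unit is 0.37 × √1.25 = 0.41 per SD of monthly practice: about 45% of the first figure and 22% of the second.

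**The case against.** The strongest objection is that nothing in the documents gives the size or sign of same-week feedback. That stands. A reader might infer that a positive result would simply be better weeks prompting practice; the documents do not support this. Without feedback there is no bias, and if worse weeks prompt practice the bias hides or reverses a benefit.

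A reader might also infer that dropping the overlapping weeks cures the problem, since rejection then returns to about 5%. That holds only if a person's state does not carry over from week to week, and zero carry-over is the most favourable case for that remedy. On its own, such a model could lend false support to a spurious result.

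The authors do plan for feedback from earlier benefit, and they deserve credit for it. Running the weighting only after a positive result suits a false-positive worry, but not a bias that can also mask an effect. Table 1 uses the cautious verb suggest, but what it suggests is still directional. Finally, concurrent monthly dose is a defensible exposure for a question about regular practice. That also stands: the overlap does not spoil the model as a description of association, only the causal reading placed on it.

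**Conclusion.** The concern holds in this form: the exposure contains the outcome's recall window for both hypotheses, feedback within that period is not addressed by the baseline covariates or by the weighting, and Table 1's reading goes further than the model can support. The overlap and the reach of the weighting follow directly from the text. The rejection rates do not: they depend on assumed correlations, carry-over and variance splits, and serve only to show that feedback too weak to notice can matter when about 435 × 12 = 5,220 person-months are analysed. They are not a forecast that this study's result will be false, or that it will err towards benefit.

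**What to change.** Keep the planned model for H1 and H2, and describe its result in Table 1 as an association. Pre-specify for both outcomes, to be run whatever the primary result:

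- (a) a sensitivity model with practice summed only over the weeks before the recall window, leaving out the last week for EQ-HWB-9 and the last two for SWEMWBS;
- (b) a model of the previous month's practice on the current outcome, adjusted for the outcome at the end of that previous month.

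State that (a) reduces but does not remove the bias if weekly state is autocorrelated, that (b) is less affected but not fully clean under strong feedback, and that both may attenuate a short-lived true effect. Use directional wording only if both agree with the primary result in sign and are not materially smaller, with that margin set beforehand. Add reverse causation to the limitations.

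The cost is two extra models per outcome on data already being collected. Model (a) gives up a quarter or half of the exposure weeks. Model (b) loses the first monthly outcome, which has no preceding month of weekly reports, leaving 11 of 12. Results are not expected before January 2028, so this can still be fixed in advance.
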